### Recruitment

Recruitment will occur through healthcare centres or hospitals during the first prenatal visit, as well as through social media campaigns and community outreach. Standard care consists of three appointments with their general practitioner or obstetrician (gestational weeks 6–10, 25 and 32), including ultrasonic scans. After the first visit, the woman will be verbally informed about the study by the healthcare professional. An informative flyer and the ACTIVE PREGNANCY Guide (online supplemental 1) will be provided, and written informed consent will be obtained to refer her to an exercise professional participating in the project. The exercise professional will provide further details on the intervention and objectives of the study, and allocation will be concealed to one of the IN or ON groups (figure 1) after checking the inclusion criteria and signing an informed consent. After inclusion, anthropometric and demographic information will be collected, along with a brief interview with the participant. The interview will provide insight into the participant’s thoughts on participating in a research project, as well as their prior and current PA levels, exercise preferences and experiences with health technologies to incorporate a patient-oriented approach into the exercise intervention. Before starting the intervention, the baseline data of the participant are measured.

### Assignment of interventions, randomisation and blinding

Blinding will be used by healthcare providers who recruit women and refer them to one of the available programmes. Exercise physiologists will generate a simple random allocation sequence stratified by study sites. Participants, healthcare providers and outcome assessors will not be blinded after assignment to interventions. Data analysts will be blinded after assignment to interventions.

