### Eligibility criteria for exercise professionals who will deliver the interventions

The exercise intervention will be carried out by graduated exercise professionals (EQF level 6 or 7), holders of a BSc, MSc or PhD in Exercise or Sport Sciences, with specialisation in exercise testing and prescription during pregnancy. Exercise professionals will explain the study’s objectives and obtain informed consent before conducting assessments and delivering the exercise intervention.

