### Exercise intervention programmes and comparators

The interventions follow international guidelines for PA during pregnancy.^7^,^9^ The exercise programme was designed and validated as a complex intervention and underwent three stages: development, pilot testing and evaluation.^14^ Exercise sessions consist of a combination of aerobic, resistance, stretching, balance, coordination, postural and pelvic floor muscle exercises, using multicomponent activities, such as aerobics, dancing, step, Pilates, bar, chair and resistance exercises using elastic bands, exercise balls, mats, dumbbells or body weight.

Table 1 describes both arms of the exercise intervention in line with the American College of Sports Medicine exercise prescription guidelines.^17^

**Table 1 T1:** Description of both arms of the exercise intervention

Arm 1:IN exercise group	Type of exercise: multicomponent prenatal exercise programme, including aerobic, coordination, strength, stretching, balance, postural and pelvic floor muscle training exercises.Duration and frequency: two sessions of 60 min per week for 12 weeks.Intensity: moderate. According to the Borg scale of perceived exertion, which ranges from 6 to 20, moderate exercise is rated between 13 and 14. Each pregnant woman will rate her perceived exertion on a scale of 6–20.IN supervision: qualified exercise physiologists.Setting: healthcare, university or fitness centres.
Arm 2:ON exercise group	Type of exercise: multicomponent prenatal exercise programme, including aerobic, coordination, strength, stretching, balance, postural and pelvic floor muscle training exercises.Duration and frequency: two sessions of 60 min per week for 12 weeks.Intensity: moderate. According to the Borg scale of perceived exertion, which ranges from 6 to 20, moderate exercise is rated between 13 and 14. Each pregnant woman will rate her perceived exertion on a scale of 6–20.Remote supervision using a virtual platform: qualified exercise physiologists.Setting: home.
	Examples of the exercise programme are continuously updated on the ACTIVE PREGNANCY YouTube channel:@GravidezAtiva-ActivePregnancy(https://www.youtube.com/channel/UC0Vyookwc0mcQ5T70imtoNA/playlists).

IN, in-person; ON, online.

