**Figure 2 F2:**
[figure not shown]
Schedule of enrolment, interventions and assessments. −t1, enrolment week; t0, allocation and baseline week; t1, pretraining assessment; t3, post-training assessment (week 12).

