### Data collection methods

Data will be collected through online (Google Forms) reliable and validated questionnaires, as well as via IN or ON field test assessments. Training for assessors will be provided to promote data quality. Table 1 includes the description of trial instruments. Data collection forms will be accessed by assessors, principal investigators (PIs) and data analysts. Data will be securely stored and managed following established ethical guidelines. Data from participants who do not complete at least 80% of the scheduled sessions will be considered a loss to follow-up.

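### The role that enrols, tests and delivers also generates the allocation list, and baseline need not precede assignment, so concealment is unprotected and arm-aware baseline error can enter the primary contrast

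*Protocol article*

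**What the plan says.** **Who makes the list.** Protocol article, Assignment of interventions, randomisation and blinding: "Exercise physiologists will generate a simple random allocation sequence stratified by study sites".

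**Who enrols, tests and delivers.** The section on eligibility criteria for exercise professionals: "Exercise professionals will explain the study’s objectives and obtain informed consent before conducting assessments and delivering the exercise intervention". Table 1 names the same profession as supervising each arm; for arm 1 it reads "IN supervision: qualified exercise physiologists", and arm 2 has the same staff working remotely. The Recruitment section has the exercise professional give the woman the details of the study at the point of enrolment.

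**Concealment.** Recruitment: "allocation will be concealed to one of the IN or ON groups", placed after the eligibility check and consent.

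**Timing of baseline.** Recruitment then describes anthropometry and an interview, and closes with "Before starting the intervention, the baseline data of the participant are measured". The Figure 2 legend gives "t0, allocation and baseline week; t1, pretraining assessment".

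**Blinding and metric.** The assignment section leaves participants, healthcare providers and outcome assessors unblinded once assigned; only data analysts are then blinded. Table 2 sets change from baseline as the metric for every primary outcome. Those outcomes are questionnaires (physical activity, self-perceived fitness) and field tests (walking distance, repetitions in 30 s, balance, flexibility, agility).

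**Testing mode.** Data collection methods says that data come from questionnaires "as well as via IN or ON field test assessments".

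**The concern.** Concealment means that whoever decides to enter a woman cannot know her next assignment. Here the list is made by the profession that holds the enrolment conversation and takes consent, and nothing in the article keeps the two tasks apart. A person who can see the list can, even without intent, influence who enters and when. Analysis cannot repair that afterwards.

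The second risk concerns measurement. If a woman and her assessor know her arm when baseline is taken, her effort, her self-report and the assessor's scoring can all depend on the arm. With a change score as the primary metric, a baseline distorted in one arm looks like a treatment difference. In an equivalence trial this can go either way: it can create a difference that does not exist, or hide one that does.

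The third matter is smaller. The sequence is described as both simple and stratified by site. Simple randomisation places no restriction on the split, so separate lists by site do not balance the arms within sites.

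**Working it through.** **1. Roles side by side**

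| Task | Role named | Section |
|---|---|---|
| Generate sequence | Exercise physiologists | Assignment of interventions |
| Inform the woman at enrolment | Exercise professional | Recruitment |
| Obtain consent, conduct assessments, deliver | Exercise professionals | Eligibility criteria for exercise professionals |
| Supervise both arms | Exercise physiologists | Table 1 |
| Blinded before assignment | Referring healthcare providers | Assignment of interventions |

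The article uses both titles for the people who deliver the programme. The only blinding before assignment covers referring providers, who do not make the list.

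**2. Order of events.** Recruitment runs: eligibility and consent, allocation, anthropometry and interview, baseline. The legend puts allocation at t0 and the pretraining assessment at t1. Neither place requires baseline before assignment.

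**3. How baseline error enters.** Let e be the mean arm-related error at baseline and δ the true difference in change. The estimated IN–ON difference in change is δ − (e_IN − e_ON), so differential baseline error passes through in full.

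**4. Illustrative size.** The article gives 100 per group and 20% loss, hence 100 × 0.8 = 80 completers per arm. Assume a differential error b, in SDs of the change score, and δ = 0. A two-sided 5% t-test then has noncentrality b√(n/2); for b = 0.2 and n = 80 this is 0.2 × √40 = 1.26.

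| Assumed b | 59 per arm | 80 per arm | 100 per arm |
|---|---|---|---|
| 0.1 | 8.4% | 9.6% | 10.8% |
| 0.2 | 19.0% | 24.2% | 29.1% |
| 0.3 | 36.6% | 47.1% | 56.0% |

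For the equivalence question, assume the margin that 80 per arm would support with two one-sided 5% tests and 80% power under true equality: (1.645 + 1.282) × √(2/80) = 2.927 × 0.158 = 0.46 SD. Equivalence is then declared when the estimate lies within ±(0.463 − 1.645 × 0.158) = ±0.203 SD. By normal approximation:

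| Assumed b | Power if arms are truly equal | False equivalence if the true difference is at the margin and b masks it |
|---|---|---|
| 0 | 80% | 5% |
| 0.1 | 71% | 16% |
| 0.2 | 50% | 35% |
| 0.3 | 27% | 59% |

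The values of b and the margin are assumptions; the article supplies neither.

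**5. Simple randomisation.** Binomial(200, 0.5) gives exactly 100:100 in 5.6% of trials, 110:90 or worse in 17.9%, and a 95% range of 86 to 114 for one arm. The effect on precision is small: at 110:90, √(1/110 + 1/90) ÷ √(2/100) = 0.1421 ÷ 0.1414 = 1.005, a 0.5% larger standard error. Within sites, whose sizes are not given, a 60:40 or worse split has probability 50% in an assumed site of 20 and 27% in an assumed site of 40.

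**The case against.** Several stronger readings are tempting, and the article does not support them.

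- **That concealment has failed.** The article asserts concealment and assigns tasks by role, not by person. It does not say that whoever makes a site's list also enrols there, and a fuller protocol may describe a mechanism. The eligibility check is in a clause that names no actor. What stands is that the overlap is stated by role and no separation is stated.
- **That baseline certainly follows allocation.** The legend calls t0 the week of both allocation and baseline, and the order within that week is not spelled out. Allocation first is the natural reading; the firm statement is that baseline is not required to come first.
- **That selection bias also passes in full into the change score.** It does not. If fitter women are steered to one arm, their baseline difference is subtracted, and only its relation to later change remains. Exclusion of women unable to take part in IN or ON formats may also limit steering by practicality.
- **That providers choose the arm.** The assignment section speaks of referral to one of the programmes, but Trial design, Participants and Sample size all state random allocation, and Recruitment has providers refer women to an exercise professional. This is loose wording.
- **That testing mode is confounded with arm.** The article allows both modes but ties neither to an arm or a visit, so this is only a possibility.
- **That simple randomisation weakens concealment or harms precision.** It is the least predictable method, the precision loss is negligible, and separate site lists may serve logistics.

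**Conclusion.** The point holds in two parts, with a minor third. First, the concealment asserted under Recruitment is not protected, because the role that generates the sequence also informs, consents, tests and delivers, and no separation is stated. Second, nothing requires baseline before assignment, although knowledge of the arm is open from then on and the primary metric is change on self-report and effort-dependent measures. Both concern what the article lays down, not detail it omits.

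The size of any bias cannot be derived from the article. The figures above show sensitivity: if differential baseline error were 0.1 to 0.3 SD of the change score, false rejection at 80 per arm would be about 10% to 47%, not 5%. They rest on those assumed errors, on 80 completers per arm and, for equivalence, on an assumed 0.46 SD margin.

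Third, the stated site stratification has no balancing effect under simple randomisation and 100 per group is not assured. The loss of precision is trivial.

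**What to change.** For all remaining enrolment (recruitment was due to start in May 2025):

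1. Have an existing team member with no recruiting, testing, delivery or blinded-analysis role, or a free central randomisation tool, generate and hold the sequence. A data analyst is a poor choice, because the article promises that analysts stay blinded.
2. Replace the simple sequence with permuted blocks of randomly varying size within site.
3. Release each assignment only after consent, eligibility and all baseline questionnaires and field tests are recorded. State this order in Recruitment and in the Figure 2 legend.
4. Record the testing mode (IN or ON) at each visit, and keep it the same for each woman at both visits where possible. A single mode for everyone would remove the question, but it could burden the remote women whom online delivery is meant to reach, so it is a trade-off and not a requirement.
5. Reword the referral sentence so that it cannot be read as providers choosing an arm.

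The cost is a short set-up of the list or tool and a small change in the order of work. No new staff are needed.

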### Outcomes

Primary, secondary and additional outcome measures, including the specific measurement variables, timeframe and instruments, are shown in table 2.

**Table 2 T2:** Primary, secondary and additional outcome measures, including the specific measurement variables, timeframe and instruments

Outcome measures	Instruments
Primary outcome measuresTimeframe: baseline (week 0) and after 12-week intervention (weeks 13 and 14)Analysis metric: change from baseline	
PA level and pattern of PA in the type of PA (work, active commuting, exercise, etc.), type of exercise, duration of each session (time spent in PA), weekly frequency and intensity and weekly volume (MET-min/week).	PPAQ^21^ and get active questionnaire for pregnancy^22^
Self-perceived fitness: self-perceived global fitness and fitness components (cardiorespiratory, strength, speed/agility and flexibility) when compared with other women of the same age. Likert scale 1 (poor) to 5 (very good).	IFIS^23^
Cardiorespiratory fitness estimated in mL/kg/min	Cardiorespiratory fitness—6-min walk test (average distance covered in metres and estimated cardiorespiratory fitness in mL/kg/min)^24^https://youtu.be/CUaFgfdSObc
Upper limbs strength	Upper limb strength—wall push-ups (number of repetitions in 30 s)^6 17^https://youtu.be/dp_tRoyxVYU
Lower limbs strength	Lower limb strength—sit-and-stand (number of repetitions in 30 s)^6 17 25^https://youtu.be/3ihcqnzyTXk
Dynamic balance	Dynamic balance—superwoman^6 17^https://youtu.be/Xiv_vWpe4-A
Static balance	Static balance—one-leg stance^6 17^https://youtu.be/sr0eYCfbLiM
Lower limbs flexibility	Lower limbs flexibility—modified sit and reach (mm)^6 17^https://youtu.be/Y6y_FAa3ulk
Upper limbs flexibility	Upper limbs flexibility—back scratch (mm)^6 17^https://youtu.be/MBwKi8kSFx8
Agility	Agility—time up and go over 3-m distance (in min)^6 17^https://youtu.be/3C944cMuTFo
Secondary outcome measuresTimeframe: baseline (week 0) and after 12-week intervention (weeks 13 and 14)Analysis metric: change from baseline	
Sleep quality	PSQI^26^
Weight prepregnancy, weight at baseline and weight gain (kg)	Body weight: measure with the participant wearing light clothing and without shoes^27^
Happiness scale	SHS^28^
Depression scale	EPDS^29^
Adherence to the Mediterranean diet	MEDAS^30^
HR	Measured rest HR, estimated maximal HR and calculated target HR (beats per minute)

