### Statistical methods for primary and secondary outcomes

Demographic data (age, weight, gestational age, area of residence and date of birth) will be described using frequencies and percentages for categorical variables.

Descriptive statistics (mean, SD, median and IQR) will be used to summarise baseline characteristics of participants in both groups (IN and ON).

Descriptive and inferential statistics will be applied to all outcomes.

A comparative analysis of IN *versus* ON interventions will be conducted using both intention-to-treat and per-protocol approaches. Comparative analysis will be used to compare changes in primary and secondary outcomes between IN and ON groups over time (baseline and postintervention). Subgroup analyses will evaluate potential differences between maternal age groups (<35 *vs* 35+ years) and PA level groups.

Adherence to the intervention (proportion of attendance in the planned sessions) will be calculated after the postintervention assessments.

Data from participants who do not complete at least 80% of the scheduled sessions will be considered a loss to follow-up.

Regarding additional outcome analysis, the evaluation of interventions and resources will be performed through descriptive analysis, summarising satisfaction with resources and exercise interventions.

Continuous variables will be assessed for normality using Shapiro–Wilk tests. Normally distributed variables will be presented as mean±SD and analysed using the independent sample t-test. The non-normally distributed data will be reported as the median with IQR and will be analysed using the Mann–Whitney test. For the within-group difference, normally distributed variables will be calculated with the paired-sample t-test. In contrast, those non-normally distributed variables will be calculated with the paired-sample non-parametric Wilcoxon test. Categorical data will be analysed using Pearson’s χ^2^ test or Fisher’s exact test, as appropriate.

A significance level of 0.05 (alpha level) will be set for all statistical tests. Power calculations were performed to ensure that the study was adequately powered to detect clinically significant differences between groups. All statistical analyses will be conducted in Statistical Package for the Social Sciences.

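### The weeks 13–14 field tests are scored by unblinded assessors from the profession that delivers the programme, with nothing that separates trainer from scorer or hides baseline scores

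*Protocol article*

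**What the plan says.** - **Blinding.** The section on assignment, randomisation and blinding states: "Participants, healthcare providers and outcome assessors will not be blinded after assignment to interventions". Only the data analysts are said to be blinded.
- **Who tests and who trains.** In the eligibility section for exercise professionals, the same profession must "obtain informed consent before conducting assessments and delivering the exercise intervention".
- **Forms.** Data collection methods states: "Data collection forms will be accessed by assessors, principal investigators (PIs) and data analysts". Under Data management, the exercise professionals enter all data.
- **Endpoint.** Table 2 sets the primary measurements at week 0 and at weeks 13 and 14, and gives "Analysis metric: change from baseline".
- **Analysis.** The statistical methods plan paired tests within each group and two-sample tests between groups. Trial design names an equivalence framework.
- **Stated safeguards.** There are two: training of assessors (Data collection methods) and blinded analysts. Limitations of the study discusses field tests against gold-standard methods and does not mention unblinded scoring.

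**The concern.** A change score is exposed to whatever differs between the two test occasions apart from the woman's fitness. By weeks 13–14 the assessor knows the arm, belongs to the profession that delivered the programme, and may have trained the woman herself. If she also sees the baseline result, she knows what figure would count as improvement. She needs no ill intent to encourage harder, or to accept a doubtful repetition.

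Two results are at stake. Scoring toward improvement would inflate the before-after tests in both arms. Scoring that depends on the arm would bias the in-person versus online comparison, which is the primary objective. That bias could produce a difference that is not there or hide one that is. Neither stated safeguard reaches the recorded score. Training improves consistency but does not mask anything, and a blinded analyst works with whatever was written down. The second safeguard is also weakened, because Data management places assessors in the group that analyses the data.

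**Working it through.** **Which primary rows are exposed.** Table 2 has ten primary rows. Two are questionnaires (physical activity and self-perceived fitness) and are not scored by an assessor. The other eight are field tests: 6-minute walk, wall push-ups, sit-and-stand, dynamic balance, static balance, two flexibility tests and agility. Most depend on effort and encouragement. In four of them (push-ups, sit-and-stand and the two balance tests) the scorer also judges what counts as a valid repetition or a loss of balance. The walk is read in metres, flexibility in mm and agility as a time, so those four are measured rather than judged.

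**Is there a plan figure to reproduce?** No. The documents give no size for scoring drift and no equivalence margin. What follows shows a range under assumptions.

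**Inputs.** Evaluable women per arm: 100 × (1 − 0.20) = 80, from Sample size. Alpha is 0.05, from the statistical methods, taken here as two-sided because the article does not say. Drift b is in SDs of the change score and is assumed. Normal approximation throughout.

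**(a) Drift shared by both arms, paired test, no true change.** Non-centrality = b√80. The rejection rate is 1 − Φ(1.96 − b√80) + Φ(−1.96 − b√80).

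| b | b√80 | False-positive rate |
|---|---|---|
| 0 | 0 | 5% |
| 0.1 | 0.89 | 15% |
| 0.2 | 1.79 | 43% |
| 0.3 | 2.68 | 77% |

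Shared drift cancels in the comparison between arms, so these rates apply only to the before-after tests.

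**(b) Drift that differs between arms, two-sample test, no true difference.** Non-centrality = b/√(2/80) = b√40, in the same formula.

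| b | b√40 | False-difference rate |
|---|---|---|
| 0 | 0 | 5% |
| 0.1 | 0.63 | 10% |
| 0.2 | 1.26 | 24% |
| 0.3 | 1.90 | 48% |

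For b = 0.1–0.2, the range is 8–19% with 59 per arm and 11–29% with 100 per arm.

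**(c) Drift toward sameness, equivalence by two one-sided 5% tests.** Take a true difference equal to an assumed margin m, with drift shrinking it to m − b. SE = √(2/80) = 0.158. Equivalence is declared when the estimate lies within ±(m − 1.645 × 0.158).

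| b | m = 0.5 SD | m = 0.3 SD |
|---|---|---|
| 0 | 5% | 3% |
| 0.1 | 16% | 9% |
| 0.2 | 35% | 16% |
| 0.3 | 60% | 20% |

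More women do not cure this. With m = 0.5 and b = 0.2, false equivalence is 28.5% at 59 per arm, 35% at 80 and 41% at 100.

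**The case against.** The strongest reply is that the article declares non-blinding openly, that participants in an exercise trial cannot be blinded, and that much of the concern fills silence in a condensed article. Several parts of this stand.

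- **Own trainees.** A reader might infer that each trainer scores her own women. The text places testing and training in one profession. It does not say who tests whom at weeks 13–14, and the pairing may be set out in the full protocol. The point is only that nothing shown prevents it.
- **Baseline scores.** A reader might infer that assessors see them at the post-test. Access to forms makes that possible, but the article does not state it.
- **Scorer judgement.** It would be too strong to say that all eight field tests rest on it. About four do.
- **Direction.** A reader might take the 10–24% as drift to the expected result. The hypothesis expects improvement in both arms and equal effectiveness between them, so a false difference is the opposite of what is expected between arms. Only (a) and (c) run with the hypothesis. No passage shows that belief in the two formats differs.
- **Adherence.** The article says: "Adherence to the intervention (proportion of attendance in the planned sessions) will be calculated after the postintervention assessments". A reader might infer that inclusion is then open to knowledge of the result. The documents do not support this. Attendance is logged during the 12 weeks and the 80% cut is fixed in advance, so the later step is arithmetic.
- **Masking the arm.** Field tests may be done in person or online. If test mode follows the arm, it reveals the arm, and full masking is not available everywhere.

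What does not stand is the appeal to condensation. Leaving assessors unblinded is a stated design choice, and the inability to blind participants does not require that trainers score or that baseline results be in view.

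**Conclusion.** The concern holds as an avoidable exposure to bias, not as evidence that bias will occur. Three facts are explicit: assessors are unblinded, the profession that trains also tests, and eight of the ten primary rows are field tests analysed as change from baseline. The possible gaps (scoring one's own trainees, sight of baseline scores) are left open by the text rather than asserted in it.

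Under an assumed shared drift of 0.2 SD of change, about 43% of paired tests in 80 women would be falsely significant. Under an assumed differential of 0.1–0.2 SD, 10–24% of comparisons at 80 per arm would show a false difference. Drift of the same size toward sameness would raise false equivalence from 5% to 16–35% if the margin were 0.5 SD. All drift sizes and margins are assumptions. The change should be made because it is cheap, and because no later analysis can remove bias from a recorded score.

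**What to change.** Amend the blinding and data collection sections to state two things.

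1. Where a site has more than one professional, or another site can run the test online, the weeks 13–14 field tests are scored by an existing professional who did not train that woman. Where the test mode allows, that professional is not told her arm.
2. Baseline scores are not visible to the assessor at the post-test.

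Where neither is possible, list unblinded assessment under Limitations of the study.

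The cost is wording, form permissions and some rescheduling among existing staff. The article does not give the number of professionals per site, so the first item is conditional; a site with one professional can still adopt the second. Changing the scorer between the two occasions adds some between-rater variation to the change score, which the planned assessor training should reduce.
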